**Fig. 1 Fig1:**
[figure not shown]
Participant timeline

### Sample size {14}

We will enroll a target enrollment sample of 3360 patients who complete the baseline SRQ and are randomized across the three treatment arms (i.e., 1120 per arm). The sample was powered to detect predictors of HTE that would increase the proportional remission rate by 20% by optimally assigning individuals as opposed to randomly assigning them into three treatment groups of equal size. A much smaller sample size would be adequate to address the first study objective of evaluating the significance of differences in aggregate remission rates across the 3 treatment arms. Meta-analyses of previous trials show that the MDD symptom remission rate averages about 25% among MDD patients randomized to ADM only and 37.5% among patients randomized to combined ADM-psychotherapy [20]. Although there were no meta-analyses of remission rates for self-guided i-CBT at the time AMHI was planned, other meta-analyses showed that effects of self-guided i-CBT were significantly better than controls [30] but worse than guided i-CBT [25, 26]. We consequently assumed, for purposes of power calculations, that the patient-centered remission rate for ADM plus self-guided i-CBT in AMHI would be 31%, which is roughly midway between the extremes. Power to detect each of the 6% differences between the extremes and the middle category using a 0.05-level 1-sided test and assuming 30% loss to follow-up (which is typical of i-CBT trials) is .86, whereas power to detect the 12.5% difference between the two extremes using the same specifications is .99.

Evaluating power to detect HTE is more complex and requires simulation. We did this by beginning with data on the observed distributions and exogenous associations among the baseline predictors in the STAR*D trial [80] and assumed that each patient was randomized across three treatment arms. We then specified a series of relatively complex nonlinear-interactive multivariate classification models for associations of these predictors with MDD remission, assuming plausible prognostic and prescriptive coefficient values that generated population distributions with the same aggregate outcome prevalence as assumed above [81]. We then modified the prescriptive coefficients to retain the aggregate remission rates while embedding HTE in the population that would result in a 20% proportional increase in the aggregate remission rate under randomization with equal allocation (i.e., from 31% to 1.2 × 31% = 37.5%). We then drew 500 pseudo-samples of different sizes from this simulated population and applied our HTE analysis method (see below) to estimate HTE in these sample data. We assumed that all the significant prognostic and prescriptive predictors were measured in the samples in addition to 20 noise predictors. Power was calculated as the proportion of replicates in which the lower bound of the 95% CI of the HTE estimate was greater than 0.0%. We also calculated proportional regret (i.e., downward bias in the estimated versus true proportional increase in remission under optimization vs. randomization). The sample size was set to yield power greater than .80 and proportional regret less than .20.

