### Objectives {7}

The first objective of AMHI is to evaluate the aggregate incremental effects of combining either best practices guided or self-guided i-CBT to ADM among patients seeking primary care treatment for MDD in West Virginia. The second objective is to determine whether stable predictors can be found of HTE in order to develop a clinical decision support system that generates an individualized treatment rule (ITR) to help patients and clinicians decide whether to add either self-guided or guided i-CBT to ADM primary care treatment of MDD. The ITR will also help identify patients for whom ADM only and combined ADM-i-CBT delivered in primary care both have low probabilities of resulting in MDD remission. A third (exploratory) objective is to use nonexperimental methods to investigate HTE with respect to two major uncontrolled aspects of MDD treatment: type of ADM; and i-CBT versus live psychotherapy (the latter obtained by 12% of primary care MDD patients in West Virginia). We hypothesize that substantial additional HTE will be documented in these nonexperimental analyses and that treatment selection across both randomized and major non-randomized aspects of treatment based on knowledge of this HTE could increase the MDD remission rate significantly.

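### The sample-size claim speaks of detecting predictors of HTE, but the simulated power is for an aggregate gain of the treatment rule; recovery or stability of predictors was not a criterion

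*Protocol article*

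**What the plan says.** All places are in the protocol article.

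- **The claim.** Sample size {14}, and the Methods part of the Abstract in the same terms: "The sample was powered to detect predictors of HTE that would increase the proportional remission rate by 20" per cent, "by optimally assigning individuals as opposed to randomly assigning them into three treatment groups of equal size".
- **The objective.** Objectives {7} gives the second aim as to "determine whether stable predictors can be found of HTE in order to develop a clinical decision support system" that produces an individualized treatment rule.
- **The criterion.** Sample size {14}, second paragraph: "Power was calculated as the proportion of replicates in which the lower bound of the 95% CI of the HTE estimate was greater than 0.0" per cent. The sample size also had to give proportional regret below .20, regret being the downward bias in the estimated proportional increase in remission. All true prognostic and prescriptive predictors were assumed measured, and 20 noise predictors were added.
- **The planned measure.** Statistical methods {20a} evaluates the rule by a CV-TMLE of the improvement in mean outcome over balanced randomization. The section on additional analyses {20b} describes Objective 2 as assessing the significance of HTE and attempting an individualized rule.

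**The concern.** The sentence that justifies 3360 patients names predictors as the thing to be detected, and Objective 2 adds that they should be stable. Neither simulation criterion scores a replicate on whether a true prescriptive predictor was found, whether a noise predictor was left out, or whether the same patient would be sent to the same arm in another sample. An aggregate gain can be clearly positive while those questions stay open.

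The Background criticises earlier studies for samples too small to give stable multivariate HTE estimates, so stability is part of what this trial offers as its advance. The rule is meant to feed a clinical decision support system. If the CI for the gain excludes zero, the current wording invites readers to attach the stated power to whichever predictors are then named.

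**Working it through.** **1. What can be reproduced.** The HTE power (above .80) comes from a simulation whose coefficients and learner library are not in the article, so it cannot be rerun. The companion aggregate figures can be checked, and they fix the number of evaluable patients.

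Inputs from Sample size {14}:
- "randomized across the three treatment arms (i.e., 1120 per arm"), with the test specified as "using a 0.05-level 1-sided test and assuming 30% loss to follow-up", so 1120 × 0.70 = 784 evaluable per arm.
- Remission "averages about 25% among MDD patients randomized to ADM only and 37.5% among patients randomized to combined ADM-psychotherapy".
- For the third arm, "ADM plus self-guided i-CBT in AMHI would be 31%, which is roughly midway between the extremes".

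Power = Φ(|p1 − p2| / √[(p1(1 − p1) + p2(1 − p2)) / 784] − 1.645):

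| Comparison | Standard error | Power | Stated |
|---|---|---|---|
| 25% v 31% | √(.4014/784) = .0226 | .843 | .86 |
| 31% v 37.5% | √(.4483/784) = .0239 | .858 | .86 |
| 25% v 37.5% | √(.4219/784) = .0232 | .9999 | .99 |

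The stated figures are reproduced closely enough to use these rates and 784 per arm.

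**2. What the HTE power refers to.** The article does not define the HTE estimate in the power criterion. Two places point to its meaning: regret is defined on the proportional increase in remission under optimization versus randomization, and {20a} evaluates the rule's improvement over balanced randomization. On that reading, power is the probability that the CI for the rule's aggregate gain over balanced randomization lies above zero.

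**3. Can that criterion be met with no predictor of HTE?** Suppose every patient has remission probability 25% on ADM only, 31% with self-guided and 37.5% with guided i-CBT, so that there is no HTE. Take the fixed rule that gives everyone guided i-CBT.

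- Mean under balanced randomization: (25 + 31 + 37.5)/3 = 31.17%.
- Gain: 37.5 − 31.17 = 6.33 points; proportionally 6.33/31.17 = 20.3%. The simulation's target was a 20% proportional increase, to 37.5%.
- As a contrast of arm means, gain = (2/3)p_guided − (1/3)p_ADM − (1/3)p_self.
- Variance at 784 per arm: [(4/9)(.375)(.625) + (1/9)(.25)(.75) + (1/9)(.31)(.69)]/784 = .14877/784. SE = .01378.
- z = .0633/.01378 = 4.60. P(lower 95% bound > 0) = Φ(4.60 − 1.96) = **.996**.
- With all 1120 per arm: SE = .01153, z = 5.50, probability .9998.

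The second criterion does not close the gap. In this no-HTE case the fixed rule is also the best rule, so its true gain is the full 6.33 points and it loses nothing to regret.

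**4. Set side by side.**

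| Question | Scored in the simulation as described? |
|---|---|
| Is the aggregate gain over balanced randomization above zero? | Yes (power) |
| How much of the true aggregate gain is estimated? | Yes (regret) |
| Are the true prescriptive predictors recovered? | No |
| Are the 20 noise predictors rejected? | No |
| Is the assigned arm stable across samples? | No |

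**The case against.** The best defence is that the sentence qualifies itself. It describes the predictors jointly, by the gain they would produce under optimal assignment, and the next paragraph discloses the exact criterion. Objective 2 seeks predictors for the purpose of building a rule, and {20a} evaluates that rule by the same kind of gain. This stands. It means that the power does address the value of the rule, and that the mismatch lies in the words about detecting predictors and about their stability.

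A reader might infer three stronger things that the documents do not support:

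- *That the power claim has no bearing on Objective 2.* It bears on the individualized-rule part, because the simulated quantity matches the planned measure.
- *That the simulation tested only for a gain above zero.* Regret below .20 was also required, although that too is an aggregate quantity.
- *That the trial has some specific low power for each predictor.* The article gives no effect per predictor and plans a super learner ensemble, not one-at-a-time interaction tests. A figure derived from such tests would rest on assumed effects, and it would have to respect the 12.5-point mean difference between guided i-CBT and ADM only.

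It is also fair to say that predictor-recovery tables and fold-agreement summaries could sit in a fuller document. Their absence from the article is not the fault. The fault is a stated power claim that goes beyond the stated criterion.

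**Conclusion.** The point holds as a mismatch between claim and criterion. The power above .80 is for an aggregate gain of the estimated rule over balanced randomization, accompanied by an aggregate limit on regret. It supports a statement about the value of the rule. It does not support a statement that predictors, or stable predictors, can be detected with that power.

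The size of the gap is shown by the no-HTE case: at the protocol's own arm rates the CI criterion is met with probability about .996 when no predictor of HTE exists.

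The conclusion assumes that the HTE estimate means the rule's gain, which is inferred from the regret definition and {20a}. The .996 further assumes a normal approximation, a fixed rule and 30% loss to follow-up; the protocol states that loss for the aggregate comparisons, and without it the probability is .9998. Nothing here shows that the sample is too small for Objective 2 as {20a} measures it.

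**What to change.** - **Reword the claim** in the Abstract and in Sample size {14}, for example: *powered to detect a gain in remission of the estimated treatment rule over balanced randomization (with proportional regret below .20); power to identify individual or stable predictors was not evaluated.*
- **Add one summary to the Objective 2 analysis:** agreement of the assigned arm across cross-validation folds or resamples. Treat named predictors as descriptive.
- **If the output of the 500 pseudo-samples was kept,** also report how often the true predictors and the truly best arm were recovered. The article does not say whether it was kept, so this part is conditional.

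Sample size, arms and the main analysis do not change. The cost is a narrower power claim and one additional summary.

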## Statistical methods

### Statistical methods for primary and secondary outcomes {20a}

The WVU analysis team will construct summary EMR variables for patients and treatment providers behind the WVU firewall and transfer these data to the survey firm via secure file transfer for linkage with the SRQ dataset behind the survey firm’s firewall. These data will be de-identified before returning to WVU and HMS for analysis. Objective 1 analyses will evaluate aggregate differences across the treatment arms. We will use logistic regression to estimate binary outcomes and report adjusted prevalence ratios with design-adjusted 95% confidence intervals (CIs). We will calculate number needed to treat (NNT) for each comparison. Generalized linear models will be used to estimate effects on continuous outcomes, making use of standard visual diagnostics to choose appropriate link functions and error structures [181]. We will report adjusted mean differences with design-adjusted 95% CIs [182].

Objective 2 analyses will evaluate HTE across the three randomized treatment arms using a special case of the super learner (SL) algorithm [183], an ensemble machine learning approach that uses cross-validation (CV) to select a weighted combination of predicted outcome scores across a collection of candidate algorithms that yields an optimal weighted combination according to a pre-specified criterion that performs at least as well as the best component algorithm. The candidate algorithms in SL can either be parametric or flexible machine learning algorithms, making SL less prone to model misspecification than traditional parametric approaches. The guarantee that SL performs at least as well as the best candidate algorithm allows a rich library of parametric and flexible candidate algorithms to be included.

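### Objective 1 power of .86 rests on a one-sided 5% test, while effects are to be reported with 95% CIs (adjacent-arm power about .75 to .78); a much smaller sample would not serve those contrasts

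*Protocol article*

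**What the plan says.** The Sample size {14} section of the protocol article sets a "target enrollment sample of 3360 patients who complete the baseline SRQ and are randomized across the three treatment arms (i.e., 1120 per arm"). HTE detection (Objective 2) drove this number. Of Objective 1 the section says: "A much smaller sample size would be adequate to address the first study objective", meaning the comparison of aggregate remission across the three arms.

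The planning rates are given next: "the MDD symptom remission rate averages about 25% among MDD patients randomized to ADM only and 37.5% among patients randomized to combined ADM-psychotherapy". For the third arm the authors assume that "the patient-centered remission rate for ADM plus self-guided i-CBT in AMHI would be 31"%. Power is then quoted for the adjacent arms ("Power to detect each of the 6% differences between the extremes and the middle category"), and the article gives its basis and value as follows: "using a 0.05-level 1-sided test and assuming 30% loss to follow-up (which is typical of i-CBT trials) is .86". For guided i-CBT vs ADM only, the article adds that "power to detect the 12.5% difference between the two extremes using the same specifications is .99".

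The second paragraph of the same section defines power for HTE as the share of simulated samples in which the lower bound of a 95% CI exceeds zero, with a target above .80.

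For the Objective 1 analysis, Statistical methods {20a} will use logistic regression and "report adjusted prevalence ratios with design-adjusted 95% confidence intervals (CIs"), with a number needed to treat for each comparison. That section mentions neither a one-sided test nor a 90% interval.

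**The concern.** Two statements in the sample size section do not fit the rest of the plan.

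First, the power basis. A one-sided 5% test is more lenient than asking a two-sided 95% CI to exclude no difference, which is a 2.5% criterion in the direction of benefit. Objective 1 power is therefore quoted on an easier scale than the one on which its results will be shown, and easier than the one the section itself uses for Objective 2.

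Second, the adequacy claim. The section says far fewer patients would do for Objective 1, then supports that objective with a power of .86 that already uses all 3360 patients.

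The adjacent contrasts (self-guided i-CBT vs ADM only, and guided vs self-guided) bear on whether the cheaper self-guided form is enough, a question that the Discussion raises. A reader who believes the trial is well oversized for Objective 1 could take an inconclusive adjacent contrast as evidence of no difference, or could regard a recruitment shortfall as harmless to that objective.

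**Working it through.** **Inputs (all from Sample size {14}).** 1120 per arm; 30% loss, so n = 1120 × 0.70 = 784 evaluable per arm; remission 25% (ADM only), 31% (self-guided), 37.5% (guided).

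**Formula.** Normal approximation for two proportions, with p̄ = (p1 + p2)/2 and Φ the standard normal distribution function:

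- SE0 = √[2p̄(1 − p̄)/n]
- SE1 = √[(p1(1 − p1) + p2(1 − p2))/n]
- power = Φ[(|p2 − p1| − z × SE0)/SE1]

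Here z = 1.645 for one-sided 5% and 1.960 for two-sided 5%.

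**Step 1: reproduce the plan's figure (one-sided 5%).**

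- 25% vs 31%: SE0 = .02268, SE1 = .02263; Φ[(.06 − 1.645 × .02268)/.02263] = Φ(1.003) = .842.
- 31% vs 37.5%: SE0 = .02397, SE1 = .02391; Φ[(.065 − 1.645 × .02397)/.02391] = Φ(1.070) = .858.
- 25% vs 37.5%: above .999.

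The stated .86 and .99 are sound on their own terms. The two differences called 6% are in fact 6 and 6.5 points. A literal 31% vs 37% would give .806, so .86 belongs to the 6.5-point contrast.

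**Step 2: same inputs, two-sided 5% (the 95% CI scale).**

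| Contrast | One-sided 5% | Two-sided 5% |
|---|---|---|
| 25% vs 31% | .842 | .754 |
| 31% vs 37.5% | .858 | .775 |
| 25% vs 37.5% | >.999 | >.999 |

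With unpooled variance the two adjacent two-sided values are .755 and .776.

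**Step 3: enrolment for 80% power.** Evaluable n per arm = [z√(2p̄(1 − p̄)) + 0.842√(p1(1 − p1) + p2(1 − p2))]² / (p2 − p1)². Divide by 0.70, round up, and multiply by 3.

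| Contrast | One-sided: evaluable per arm → total enrolled | Two-sided: evaluable per arm → total enrolled |
|---|---|---|
| 25% vs 31% | 692 → 989 × 3 = 2,967 | 878 → 1,255 × 3 = 3,765 |
| 31% vs 37.5% | 659 → 942 × 3 = 2,826 | 836 → 1,195 × 3 = 3,585 |
| 25% vs 37.5% | 169 → 242 × 3 = 726 | 215 → 308 × 3 = 924 |

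As shares of 3360, the one-sided needs for the adjacent contrasts are 2,967/3360 = 88% and 2,826/3360 = 84%. The two-sided needs exceed 3360.

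**Step 4: what a smaller trial would give, even one-sided.** With half the enrolment (1,680; 392 evaluable per arm), power is .59 and .61. With three quarters (2,520; 588 per arm), it is .74 and .76.

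**Step 5: where the adequacy sentence is true.** A 2-df omnibus chi-square test of the three rates needs about 264.4 evaluable per arm for 80% power, so 3 × 264.4/0.70 ≈ 1,133 enrolled; at 784 per arm its power is .999. Guided i-CBT vs ADM only needs 924 two-sided. Both are about a third of 3360 or less.

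**The case against.** The strongest reply is that nothing here is miscalculated. The test is disclosed as one-sided, the .86 reproduces, and Trial design {8} frames the aim as superiority of each i-CBT arm over ADM only. Reporting a 95% CI beside a directional test is not in itself a contradiction. The methods section says the intervals will be reported; it does not make them the decision rule. The .80 target is stated only for HTE, so .75 breaches no declared Objective 1 threshold. All of this stands. A reader might infer that the .86 is an arithmetic error, or that the plan commits itself to judging Objective 1 by whether the 95% CI excludes no difference. The document supports neither. What remains is that the only uncertainty scale named for Objective 1 results is the 95% CI, and that the section's other power criterion is a 95% CI bound.

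A second reply is that the adequacy sentence speaks of differences across the three arms, which an omnibus test would cover with about 1,133 patients. That reading is possible, so calling the sentence false outright would go too far. But the sentence is not limited to that test, and the power offered for the objective is pairwise, for each adjacent difference.

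A reader might also infer that the three contrasts lack error control. An article whose statistical analysis plan is not shown cannot establish that, since multiplicity may be handled there. Nor does it give any basis for assuming that remission on the composite measure is lower than the planning rates.

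Finally, the planned analysis is covariate-adjusted and inverse-probability weighted. Adjustment could raise power and weighting could lower it, and the document quantifies neither.

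**Conclusion.** The point holds at moderate severity, as a mismatch between the basis for power and the planned reporting, together with an adequacy claim that is too broad. On the 95% CI scale, power for the adjacent contrasts is about .75 (25% vs 31%) and .77 to .78 (31% vs 37.5%) against the quoted .86; guided i-CBT vs ADM only is unaffected.

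The adequacy claim fails for the adjacent contrasts under either sidedness, so that part needs no assumption about how results will be judged. The lower power figures do need one: that readers will take the 95% CI as the standard of evidence, which is natural but inferred. All figures are unadjusted approximations with the plan's own rates, 30% loss, equal allocation and no multiplicity adjustment.

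**What to change.** In Sample size {14}:

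- State two-sided 5% power of about .75 for 25% vs 31%, .77 to .78 for 31% vs 37.5%, and above .99 for 25% vs 37.5%, alongside or in place of the one-sided figure.
- Describe the adjacent differences as 6 and 6.5 percentage points.
- Limit the sentence on a much smaller sample to guided i-CBT vs ADM only or to an omnibus test of the three arms, or delete it.

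Optionally, if the statistical analysis plan does not already settle multiplicity, name a closed order: the 2-df global test first, then each pairwise contrast at two-sided 5%. With three arms this controls family-wise error, and the global test has power of about .999 under the planning rates.

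The cost is wording only. The stated power looks less favourable; enrolment does not change, because HTE set the sample size.

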### Recruitment {15}

We anticipate a 24-month recruitment period. As outlined in Table 4, initial eligibility will be determined during the patient’s clinic visit. Potentially eligible participants will be provided with a study fact brochure, which contains highlighted study information as well as the study website URL and an 800 number for additional questions. Participating clinics will then gain permission from eligible participants to provide AMHI study staff with their contact information. Eligible participants who were not informed (i.e., missed in recruitment) will be sent a letter explaining the study along with a study fact brochure under the signature of their treating clinician. This letter will contain the study 800 number for patients who would prefer to opt out. Patients who do not opt out will receive a telephone call from AMHI study staff to reassess eligibility, review material in the study fact brochure, and answer patient questions before seeking electronic informed consent to participate in the study. Patients who prefer to physically sign the informed consent will be mailed two hard copies (one for their records) along with a pre-addressed pre-stamped return envelope.

**Table 4 Tab4:** Participant recruitment

